**Randomised Controlled Trial**			
*Primary*			
Difference in the percentage of well controlled asthma-like symptoms after 1-year follow-up	I	TRACK-score	Unpaired t-test / Mann Whitney-U test
*Secondary*			
Pharmacotherapy	I, II, III, IV	Cumulative ICS dosage (fluticasone equivalent)	Mann Whitney-U test
Growth retardation	I, II, III, IV	SD deviation from target height	Unpaired t-test
Amount of exacerbations	I, II, III, IV	Amount	Chi-square test
Amount of hospital admissions	I, II, III, IV	Amount	Chi-square test
Quality of life child	I, II, III, IV	EQ-5-DY by proxy	Unpaired t-test / Mann Whitney-U test
Quality of life caretaker	I, II, III, IV	EQ-5-DY	Unpaired t-test / Mann Whitney-U test
Lung function (tremoflo)	I, II, III, IV	R_5_, R_5-20_, X_5_, X_5-20_, AX, F_res_ (baseline and % change after salbutamol)	Unpaired t-test / Mann Whitney-U test
Lung function (spirometry)	II, III, IV	FEV_1,_ FVC, MEF50 (baseline and % of change after salbutamol)	Unpaired t-test / Mann Whitney-U test
Absence of school and work (parents)	I, II, III, IV	Number of days	Chi-square test
Healthcare resource use and –costs	I, II, III, IV		Unpaired t-test / Mann Whitney-U test
Costs outside healthcare	I, II, III, IV	Euro	Unpaired t-test / Mann Whitney-U test
Cost-effectiveness	I, II, III, IV	Societal cost per QALY and health care cost per additional child with control of asthma-like symptoms	Sensitivity and bootstrap analysis

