### Hypotheses of the ADEM2 study

The hypothesis of the clinical trial of the ADEM2 study is that application of the breath test in preschool children with asthma-like symptoms will result in important health gain and reduction of costs of care. In children with asthma, we expect that an early diagnosis by the breath test will result in more targeted and better treatment. This will facilitate better asthma control, improved lung function, less exacerbations, less hospital admissions, improved quality of life, and probably less airway remodelling. In children with transient wheeze, we hypothesise that an early diagnosis will diminish uncertainty of parents and treating doctors, with less referrals, less additional examinations (X-rays, allergy tests, microbial cultures or viral PCR tests), and less ineffective treatment (antibiotics, corticosteroids, or antihistamines). Parents will be reassured by the early diagnosis of transient wheeze, which will probably increase quality of life and decrease medical consumption. In both cases, cost savings are expected because of a proper diagnosis by the breath test due to significantly reduced hospital based care and medication use in children with transient wheeze, and prevention of undertreatment related sequela in children with asthma.

Our hypothesis of the observational cohort study with respect to the feasibility, reproducibility and accuracy of the alternative VOC-sensing techniques is that innovative techniques such as SIFT-MS are not inferior to the current golden standard GC–MS. We also hypothesise that new (combinations of) biomarkers will be found that improve the diagnostic accuracy to identify the wheezing preschool child developing asthma, such as epigenetic signatures of blood eosinophils, microbiome data of both nasopharyngeal swabs and faecal samples, whole RNA sequencing on blood, gene-expression of relevant asthma genes, and immunological markers.

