### Outcomes

#### Randomised controlled trial

Primary outcome: difference between the intervention group and the usual care group in the percentage of well controlled asthma-like symptoms after 1- and 2-year follow-up. The percentage well controlled asthma-like symptoms will be based on the validated TRACK questionnaire.Secondary outcomes: differences after one year and at the end of the study between the intervention group and usual care group will be assessed with respect to:Number of exacerbationsLung function (spirometry) at 6 years of ageAirway resistance with forced oscillation techniqueQuality of life of children and their parentsPharmacotherapy (frequency and dosage of used medication)Growth velocity over 12, 24 and 36 months (cm/y), change in height SD scores over 12, 24 and 36 monthsPatient reported side-effects of medicationHealthcare resource use and –costs (standard and extra clinical visits, hospital admissions, referrals, laboratory tests, imaging tests)Costs outside healthcare (over-the-counter drugs)Absence of school and work (parents);

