### Participant timeline

Both wheezing participants and healthy participants follow the same timeline (Fig. 1). Participants enrol in the study, after informed consent, at the age of 2 or 3 years old. At the baseline visit, the wheezing children that participate in the RCT will be randomised into either the intervention group or the usual care group. All children included in the study will perform the study-related procedures, including the breath test, at the baseline visit (see section “data collection” and Fig. 2). The children that will be allocated to the intervention arm of the RCT will receive their probability diagnosis and corresponding treatment advice within three months of the baseline visit. All children will be invited for the annual, study-related hospital visits until the age of 6. The performed study procedures at each visit are illustrated in Fig. 2. All parents will receive online questionnaires prior to the annual visit (a list of the questionnaires is provided in Fig. 3). Parents of children that participate in the RCT will also receive questionnaires on disease control and healthcare related expenditures with a 3-month interval. At the age of 6, a final diagnosis will be made based on respiratory symptoms, use of medication, and objective lung function measurements as reported previously [22].

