### Pharmacotherapy

Use of asthma medication and antibiotics will be continually registered: drugs, dosage, and period of use. Parents will be asked to register this using the app “Qdot studies” developed by Maastricht University. This app is specifically designed to collect data for scientific studies through questionnaires. We will assess whether children with asthma get bronchodilators (for symptom relief) and maintenance use of ICS (in case of more severe symptoms and less controlled disease) according to (inter) national guidelines [29], and look for differences in proper treatment of asthma between intervention and control group.

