A cost-effectiveness analysis will be performed from a societal and healthcare perspective with a time horizon of 2 years. Incremental cost-effectiveness ratios will be calculated as societal cost per QALY (societal perspective) and health care cost per additional child with control of asthma-like symptoms (healthcare perspective). Standard sensitivity- and bootstrap analysis will be performed to address uncertainty regarding costs and cost-effectiveness outcomes. Cost-effectiveness acceptability curves will be constructed reflecting the probability that the diagnostic breath test is cost-effective for a range of threshold values. Costs and effects after one year will be discounted at 4.0% and 1.5% respectively, according to the Dutch guidelines for health economic evaluation [45, 48].

All outcome parameters and corresponding outcome measures and methods of analysis are listed in Table 2. The large number of patients (*n* = 220) allows better representation of specific subgroups of specific age, background (primary or secondary/tertiary care), genetic predisposition, and geographic area. All these parameters will be measured and included in the multivariable analysis in order to assess possible influences on outcome. Intention-to-treat analyses will be applied. We will execute two subgroup analyses: one for age and one for level of care (first-line versus secondary/tertiary care). Two-sided *p*-values < 0.05 (with correction for multiple testing) will be regarded as statistical significant.

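### Table 2 measures pharmacotherapy by cumulative ICS dose alone: antibiotic use, named in the hypothesis and recorded, has no planned comparison, and the end-of-study total depends on follow-up length

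*Protocol article*

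**What the plan says.** - **Hypothesis.** In children with transient wheeze, an early diagnosis is expected to lead to "less ineffective treatment (antibiotics, corticosteroids, or antihistamines". For children with asthma, "we expect that an early diagnosis by the breath test will result in more targeted and better treatment" (Hypotheses of the ADEM2 study).
- **Outcome.** Under Outcomes, Randomised controlled trial, pharmacotherapy is a secondary outcome covering both how often medicines are used and at what dose. For the secondary outcomes, "differences after one year and at the end of the study between the intervention group and usual care group will be assessed".
- **Data.** "Use of asthma medication and antibiotics will be continually registered: drugs, dosage, and period of use" (Pharmacotherapy). The same section says the study will check whether children with asthma receive relievers and maintenance ICS according to guidelines, and "look for differences in proper treatment of asthma between intervention and control group".
- **Analysis.** The pharmacotherapy row of Table 2 gives "Cumulative ICS dosage (fluticasone equivalent", a Mann-Whitney U test and analysis groups I to IV. It states no window and no division by time observed.
- **Completeness.** "All outcome parameters and corresponding outcome measures and methods of analysis are listed in Table 2".
- **Follow-up.** "Participants enrol in the study, after informed consent, at the age of 2 or 3 years old" (Participant timeline). Follow-up ends at age 6.

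**The concern.** The breath result can help a child only through what doctors and parents then do, and prescribing is the most direct sign of that. The Discussion itself names a small contrast between the arms as a possible pitfall. Two features of the Table 2 row weaken the outcome that would show such a contrast.

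First, the row is narrower than both the outcome and the hypothesis. Frequency of use has gone. Antibiotics, which are named in the hypothesis and registered in the app, have no measure and no test. Antihistamines, also named, have no row and are not among the drugs the Pharmacotherapy section says are registered.

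Second, a total dose grows with time observed. At the end of the study that time differs between children by design, and a child who leaves early looks like a low user.

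**Working it through.** **1. Hypothesis, data and analysis side by side**

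| Drug class in the transient-wheeze hypothesis | Registered in the app | Own measure in Table 2 |
|---|---|---|
| Corticosteroids | Yes, as asthma medication | Yes, for the inhaled form |
| Antibiotics | Yes | No |
| Antihistamines | Not named | No |

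One of three named classes has its own measure. For antibiotics the gap lies only in the analysis; for antihistamines it may also lie in the data. The 3-monthly resource questionnaire asks about medication, including over-the-counter products, and might capture them.

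**2. Range of follow-up**

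Follow-up = 6 − age at entry. Entry at the 2nd birthday gives 6 − 2 = 4 years. Entry just before the 4th birthday gives just over 6 − 4 = 2 years. At a constant daily dose the totals differ by a factor of up to 4 / 2 = 2, whatever the dose. At one year the window is the same for every child, apart from dropout and missing records.

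**3. Does this bias the comparison of arms?**

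The document gives no distribution of entry ages. Assume follow-up uniform on 2 to 4 years:

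- mean 3 years; SD = 2/√12 = 0.577 years; coefficient of variation (CV) = 0.577/3 = 19%;
- 95% range of the chance difference in mean follow-up, 110 per arm: 1.96 × 0.577 × √(2/110) = ±0.15 years, or 0.15/3 = 5%.

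Randomisation balances follow-up in expectation, so entry age adds variance and not bias.

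**4. What the added variance costs**

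The document states no power for this outcome. Its planned total of 220 less 10% dropout leaves 198, or 99 per arm. With that number, Mann-Whitney at two-sided 0.05 and 3,000 runs per setting, cumulative dose was compared with dose per year on the same simulated children. Assumed, not in the document: lognormal annual dose among users (CV 0.5 or 1.0), 0% or 30% non-users, and true dose ratios of 1, 0.75 and 0.65.

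Rejection rate, cumulative / per year:

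| CV, non-users | Ratio 1 | Ratio 0.75 | Ratio 0.65 |
|---|---|---|---|
| 0.5, 0% | 0.055 / 0.054 | 0.970 / 0.982 | 1.000 / 1.000 |
| 0.5, 30% | 0.056 / 0.056 | 0.452 / 0.503 | 0.769 / 0.829 |
| 1.0, 0% | 0.053 / 0.051 | 0.635 / 0.659 | 0.931 / 0.943 |
| 1.0, 30% | 0.055 / 0.056 | 0.209 / 0.223 | 0.382 / 0.396 |

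The simulation standard error at 5% is √(0.05 × 0.95/3000) = 0.004, so type I error is compatible with 5% throughout. The power gain from scaling by time runs from 0 to 6 points.

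**5. Dropout**

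The protocol allows for 10% dropout and cites 2% loss in the earlier ADEM study; neither figure is split by arm. As an illustration, suppose all loss falls in one arm, at one year, with a 3-year mean otherwise:

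- 10% lost: 0.90 × 3 + 0.10 × 1 = 2.80 years, which is 6.7% below 3;
- 2% lost: 0.02 × 1 + 0.98 × 3 = 2.96 years, which is 1.3% below 3.

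At equal prescribing, the mean total dose in that arm would fall by the same percentage.

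**The case against.** Several points on the other side are sound.

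- **Corticosteroids are covered in part.** A reader might infer that the hypothesis names systemic steroids and that Table 2 omits them. The text says corticosteroids without that qualifier, and ICS belong to the class.
- **Relievers are not ignored.** The Pharmacotherapy section plans to compare guideline-conform treatment in children with asthma, bronchodilators included. That comparison has no row in Table 2, but it is stated. It does not help with antibiotics, where the prediction concerns transient wheeze.
- **Medication also enters the costs.** Medication, including over-the-counter products, is valued in the cost analysis. That puts antibiotics into a euro total; it does not compare their use.
- **Two-fold between children is not two-fold between arms.** This stands, as steps 3 and 4 show. Age is also to be entered in a multivariable analysis, which could absorb part of the noise from entry age, though not the effect of early leaving.
- **The article is condensed.** Windows and scaling by observed time are often settled in the analysis plan, and the Outcomes section does set the assessment times. This lowers the weight of the window point. It does not dispose of the antibiotic point, because the article itself calls Table 2 complete. The article also shows that it can fix such detail: growth velocity is given per year over 12, 24 and 36 months.

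**Conclusion.** The point holds, at modest weight for a secondary outcome. Table 2 does not carry the pharmacotherapy outcome as defined, and one prediction of the hypothesis, less antibiotic use, has no planned test although the data are collected. Antihistamines are named in the hypothesis with no measure and no assured data source.

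The accumulation window is the smaller part. It concerns the end-of-study comparison, where it costs 0 to 6 points of power under the assumed dose and entry-age distributions. It would bias the comparison only if dropout or recording differed between arms. Families and doctors know the allocation and parents do the recording, so this is possible, but the document gives no evidence of it.

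A reader might conclude that the treatment hypothesis as a whole goes untested. The document does not support that: ICS dose is tested, with a common window at one year, and a comparison of asthma treatment is described in the text.

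**What to change.** In the pharmacotherapy row of Table 2:

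1. Replace the cumulative total by ICS dose per observed day (fluticasone equivalent) over 0 to 12 months from randomisation, and over either 0 to 24 months or the full period divided by observed days. The 24-month window is open to every child, since all enter before age 4. It is also easier to interpret than the full-period average, which covers ages 2 to 6 in the earliest entrants and only 4 to 6 in the latest. Define observed days as those covered by a medication record, so that a gap is not read as non-use.
2. Add a row for antibiotic courses per observed year over the same windows.
3. For antihistamines, use the 3-monthly questionnaire if it captures them, and give them a row; otherwise remove them from the hypothesis.

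This is table wording and uses data already collected, apart perhaps from antihistamines. The downside is more secondary tests under the multiplicity correction already planned. If each of groups I to IV counts as one comparison, an antibiotic row adds four per window, or eight over two windows.

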### Sample size

*Randomised controlled trial* With a presumed percentage of well-controlled preschool children with asthma-like symptoms of 20% in the usual care group (based on reference [32, 33]), and of 40% in the intervention group, 91 patients in both groups are needed to detect this difference with an alpha of 0.05 and a power of 80%. Taking a dropout rate of 10% into account, we aim to include a total number of 220 preschool children with asthma-like symptoms.

*Prospective cohort study* For studies assessing the relationship between microbiome, transcriptomics, epigenetics, and atopic outcomes like asthma, a sample size of 70–80 is considered adequate [34, 35].

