### Data collection

During the annual visits, various study procedures will be conducted. Each centre in which the study visits take place (the “measurement centres”) has a dedicated team consisting of one or two research nurses, and one or two p that execute all study-related procedures. All study personnel will be trained in the study requirements and study procedures. Standard Operating Procedures (SOPs) will be provided to all study sites to enhance data quality and reduce variability in measurements as much as possible.

Parents will be instructed that their children should refrain from eating, brushing teeth, using inhalation medication, and moderate to severe exercise as much as possible within 60 min prior to the visit. Drinking of water is allowed prior to the tests. Prior to the annual visits, electronic questionnaires will be sent to the parents. In the RCT study group, a subset of these questionnaires will also be sent at three monthly intervals. The parameters that are measured are listed in Fig. 2.

A web-based study management system Ldot (https://nl.ldot.nl/) will be used to monitor the study logistics and guard the process of the research project. Ldot enhances participant retention by sending both automatically generated reminders for study personnel to contact patients, and automatically generated reminders to study participants to attend planned visits (both by e-mail and SMS messages). Also, periodic communications via newsletters and a website will be provided to parents, recruiting doctors, and treating doctors of participating patients.

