### Growth

Weight and height will be assessed in height standard deviation (SD) z-scores according to national growth data. Height velocity will be calculated.

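### Table 2 tests growth with a measure that the Outcomes section does not define, and gives no analysis for the two growth measures that it does define

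*Protocol article*

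**What the plan says.** Three places in the protocol article bear on growth.

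- **Outcomes, randomised controlled trial.** Among the secondary outcomes, growth is given as height velocity in cm per year and as change in height SD score, both at 12, 24 and 36 months.
- **Growth (Methods).** "Weight and height will be assessed in height standard deviation (SD) z-scores according to national growth data". The next sentence adds: "Height velocity will be calculated". The reference is the national growth data. Change in z-score is not mentioned here; velocity is.
- **Table 2, row on growth retardation.** The only measure is "SD deviation from target height", compared by unpaired t-test in analysis groups I to IV.

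The section on health gain and costs then states the status of that table: "All outcome parameters and corresponding outcome measures and methods of analysis are listed in Table 2".

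**The concern.** Two sections point to growth over time against national references. The table that is declared complete points to the distance from a different reference, target height, and does not say when it is taken or whether baseline is used. Whoever writes the analysis cannot follow both. Followed as written, the table leaves the defined outcome unanalysed and tests one that was never defined. If the choice stays open, it may be made after the data are seen.

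The Background names reduced linear growth as a side effect of inhaled corticosteroids, and overtreatment is one of the two problems that the breath test is meant to reduce. Growth is therefore a secondary outcome that readers will look for. A single-visit distance from target also carries all the height differences that the children already had at entry, which a change from baseline largely removes.

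**Working it through.** **1. The plan's own figure.** The only design figure is for the primary outcome: 20% against 40% well controlled, two-sided 5%, 80% power, 91 per arm (Sample size). The pooled formula gives [1.960·√(2·0.3·0.7) + 0.842·√(0.2·0.8 + 0.4·0.6)]² / 0.2² = 81.2, so 82; with the continuity correction it is 91, as stated. Nothing below alters this. No SD, correlation or effect size is given for growth.

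**2. The growth definitions side by side.**

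| | Outcomes | Growth section | Table 2 |
|---|---|---|---|
| Measure | velocity; change in height SD score | height z-score; velocity | deviation from target height |
| Reference | not stated | national growth data | target height, not defined in the visible text |
| Times | 12, 24, 36 months | none | none |
| Change over time | yes, both | velocity only | not stated |

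**3. Two readings of the Table 2 row.** Let H1 and H2 be a child's height SD score at baseline and follow-up, and T the target-height SD score, fixed within a child.

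- Change in deviation: (H2 − T) − (H1 − T) = H2 − H1. This is the change in height SD score, so nothing is lost and the row is only misworded.
- Deviation at one visit: H2 − T. Baseline differences between children remain in it.

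**4. Precision under the single-visit reading.** Assumed inputs: 99 per arm (220 less 10%, halved), taking group I to be the full randomised comparison; SD of height SD score 1; SD of target-height SD score 0.75; child-target correlation r from 0.4 to 0.6; between-visit correlation ρ from 0.5 to 0.95.

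- Detectable difference at 80% power = (1.960 + 0.842) × SD × √(2/99) = 0.398 × SD.
- SD of deviation = √(1 + 0.75² − 2·r·0.75): 0.98 at r = 0.4, 0.90 at 0.5, 0.81 at 0.6. Detectable difference: 0.39, 0.36, 0.32.
- SD of raw change = √(2(1 − ρ)). Residual SD with baseline as covariate = √(1 − ρ²).

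| ρ | SD, raw change | Detectable, raw change | Detectable, baseline-adjusted | Deviation (0.32–0.39) ÷ raw change |
|---|---|---|---|---|
| 0.95 | 0.32 | 0.13 | 0.12 | 2.6–3.1 |
| 0.90 | 0.45 | 0.18 | 0.17 | 1.8–2.2 |
| 0.80 | 0.63 | 0.25 | 0.24 | 1.3–1.6 |
| 0.70 | 0.77 | 0.31 | 0.28 | 1.1–1.3 |
| 0.60 | 0.89 | 0.36 | 0.32 | 0.9–1.1 |
| 0.50 | 1.00 | 0.40 | 0.34 | 0.8–1.0 |

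The advantage of a raw change score is large at ρ of 0.9 or more, modest at 0.8, small at 0.7, and gone or reversed at about 0.6 and below. With baseline as covariate, the defined measure is still at least as precise at 0.6 and lies inside the range for deviation at 0.5.

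**The case against.** The best defence is that this is a terse table row for one secondary outcome. Other rows are as short, and the row may mean change in deviation from target, which equals change in height SD score. The same section also has a general rule, t-test or Mann-Whitney U test for continuous variables, that could be applied to velocity and change. An unpaired t-test on change scores is valid, and covariates are often left to the analysis plan. All of that is fair. It does not settle which measure is the outcome or at what times, and the article itself calls the table complete. If change in deviation is meant, the row still needs rewording.

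A reader might go further and infer three things that the documents do not support.

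- **That parental heights, which the usual mid-parental target height would need, are not collected.** Data collection says "The parameters that are measured are listed in Fig. 2", and Participant timeline says "a list of the questionnaires is provided in Fig. 3". Neither figure is in the text at hand. One can say only that the visible text neither mentions parental height nor defines target height.
- **That the Table 2 measure is two to three times less sensitive, so a real effect would be missed.** That ratio needs the single-visit reading and a between-visit correlation of about 0.90 to 0.95, both assumed. A claim about missed effects also needs an effect size, and none is given.
- **That the comparison is biased by height differences at entry.** Allocation is random, so those differences cost precision only.

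**Conclusion.** The contradiction stands: Outcomes defines velocity and change in height SD score, the Growth section plans national z-scores and velocity, and Table 2 tests neither. It is more than omitted detail, because the text says that the table covers every measure and method.

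The loss of precision is probable but conditional. On a single-visit reading with the assumptions above, the detectable difference is 0.32 to 0.39 SD score for deviation from target, against 0.13 to 0.18 for change at correlations of 0.95 to 0.90, 0.25 at 0.8 and 0.31 at 0.7. There is no gain for a raw change score at about 0.6 or lower, and no loss at all if the row means change in deviation. The primary outcome and the sample size are unaffected.

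**What to change.** In the Table 2 growth row, replace the present measure by the two in Outcomes: change in height SD score (national reference) and height velocity, each at 12, 24 and 36 months. Compare the arms with baseline height SD score as covariate; the covariates now named for the multivariable analysis do not include it. Keep deviation from target height only as a descriptive measure, with its definition and time point stated, and only if parental heights are collected.

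The cost is one table row and matching wording in the analysis plan. The defined outcomes already require baseline and follow-up heights, so no new measurement is needed. The change should be made before the arms are compared on growth.
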